### Data collection and management

Medical records of the participating hospitals serve as the source data, including clinical information and laboratory values, which are accessible and maintained in accordance to national standards and regulations. Outcome data will be extracted from participant’s clinical notes and laboratory reports into an electronic case record form (CRF). For long-term storage, clinical data will be electronically archived at Faculty of Medicine, Chiang Mai University, Thailand, as per the regulatory requirements for good clinical practice and in line with the Medical Research Council requirements and local policies.

The questionnaires will be completed by the patient. For those with literacy problems, the questionnaires will be read out to the participant, the participant will respond to each question and their responses will be recorded by the staff member administering the questionnaires.

Trial data will be captured in a Research Electronic Data Capture (REDCap), secure SQL server database. An independent data monitoring committee (DMC), including both local and international experts, has been appointed and convened. Interim analyses of major outcome measures and safety data will be conducted and provided in strict confidence to the DMC. Any decision to stop the trial early will be based on the balance of efficacy and safety.

### Sample size and power calculations

Most recent studies suggest that the mean TTR in Thai patients receiving warfarin is in the range of 50%–55%.^11 12^ Since an improvement of 10% in the mean TTR is likely to be clinically meaningful, we assume a 10% difference in 12-month TTR with 90% power and 5% significance level for our sample size calculation and using an SD of ‘26’ as observed in a previous Thai study to determine the sample size estimates. Hence, to detect a 10% mean difference in TTR at 12 months, using two-sided test, sample size for randomisation in a 1:1 ratio would be 288 or 144 per arm. Assuming and adjusting for a 10% attrition/loss to follow-up rate, a total sample size of 320 patients or 160 per arm is needed.

### Statistical analysis

Continuous variables will be presented as mean (SD), or median (IQR), as appropriate; categorical variables will be reported as counts with percentages. Descriptive statistics will be presented for baseline demographic and clinical information. For all major outcomes, summary statistics and differences between groups (eg, mean differences and relative risks) will be presented, with CIs and p values from two-sided tests also given.

All analyses will be based on the intention-to-treat (ITT) principle. The primary comparison groups will be composed of those randomised to Group 1, usual care, versus those randomised to Group 2, the SAMe-TT_2_R_2_ score-guided strategy with the TREAT intervention (plus usual care). All outcomes will be adjusted for the stratification variables (centre, sex and baseline SAMe-TT_2_R_2_ score) where possible. Two-tailed p values <0.05 will be considered statistically significant. No adjustment for multiple comparisons will be made.

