### Eligibility criteria

Patients must meet all of the following inclusion criteria to be eligible for randomisation:

≥18 years of ageNewly diagnosed patients with non-valvular AF.ECG-documented AFWarfarin eligible (men with CHA_2_DS_2_VASc score ≥1; women with CHA_2_DS_2_VASc score ≥2)Warfarin naïve (no treatment with anticoagulation within the past 12 months; treatment may have started within the prior 28 days from randomisation).Able to comply with scheduled visits, treatment plan and laboratory testsAble to give informed consent and comply with study protocol (with support of a carer)

Patients will be excluded from participation if they present with any of the following:

Any contraindication to oral anticoagulationProsthetic cardiac valve or significant valvular heart disease with an indication for heart surgeryLikelihood of intermittent or permanent discontinuation of warfarin during follow-up (eg, major surgery or post-AF ablation)Known active malignancy with a life expectancy less than 5 years.Diagnosed significant cognitive impairment preventing provision of informed consent and/or able to comply with the study protocol.Any disease likely to cause death within 12 months.

The study was originally designed to enrol the patients within 5 days of warfarin treatment; however, the average referral time was 14 days. The trial steering committee agreed to extend the duration between starting warfarin and randomisation to 28 days to improve recruitment rate, external validity and generalisability of the trials. The amended study protocol was approved by the Institutional Ethical Committee of each study site and by the IRB of the Ministry of Public Health, the Royal Government of Thailand and updated in the Thai Clinical Trials Registry.

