**Follow-up of clinical events:** TTR, composite of thromboembolism, major bleeding and all-cause death (in all patients)					
	**Baseline**	**M1±7D**	**M2±7D**	**M6±14D**	**M12±14D**
Clinical assessment	**a, b, c, d**	**c**	**c**	**c**	**c, d**
ECG	x				
INR**	x	x	x	x	x
Standard OAC therapy education	x				
TREAT intervention		x			
Questionnaires	x			x	x
Qualitative assessment	x†			x	
Health economic assessment	x			x	x
Follow-up of clinical events				x	x

*INR monitoring is mandatory during the 12-month follow-up period for all patients, with frequency as per usual care conducted by anticoagulation clinics.

†Baseline interviews of patients will take place within 4 weeks of receiving the intervention.

AF, atrial fibrillation; CABG, coronary artery bypass grafting; COPD, chronic obstructive pulmonary disease; ECG, electrocardiogram; EQ-5D-5L, The 5-level EQ-5D version; INR, international normalised ratio; OAC, oral anticoagulants; PCI, percutaneous coronary intervention.

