#### Analysis of outcome measures

##### Primary outcome

The primary outcome is the TTR at 12 months and differences in TTR between the intervention and usual care groups will be examined using a linear regression model. Results will be presented as mean difference and 95% CI. A key assumption for this analysis is that the data will be normally distributed; this assumption will be examined visually based on the residuals from the fitted model. If data are deemed not to be normally distributed, then the Mann-Whitney U test will be used for analysis.

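### The TTR model adjusts only for the stratification factors; prespecifying the INR at randomisation as a further covariate may give a small, conditional gain in precision

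*Protocol article*

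**What the plan says.** The covariates are set under Statistical analysis in the protocol article: "All outcomes will be adjusted for the stratification variables (centre, sex and baseline" SAMe-TT2R2 score is the third, and the sentence is qualified by where this is possible). They are the same factors that stratify the randomisation. Under Primary outcome, "differences in TTR between the intervention and usual care groups will be examined using a linear regression model". If the residuals look non-normal, the Mann-Whitney U test replaces the regression. Continuous secondary outcomes, which include TTR at 6 months, are analysed in the same way.

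Two other places bear on the point:

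- Eligibility criteria: "treatment may have started within the prior 28 days from randomisation". The window was 5 days before the amendment, and the average referral time is given as 14 days.
- Table 2: the INR row is marked at baseline as well as at months 1, 2, 6 and 12. The footnote, "INR monitoring is mandatory during the 12-month follow-up period for all patients", concerns monitoring after entry. It is the row, not the footnote, that shows a baseline INR.

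**The concern.** After the amendment, one patient may be randomised on the first day of warfarin and another after four weeks of dose adjustment. Their INRs at entry can differ for that reason alone. An INR taken at randomisation belongs to the same process that TTR later summarises, so it is a natural candidate for a baseline covariate. Centre, sex and score do not directly describe how far titration has gone.

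If that INR predicts TTR, leaving it out keeps explainable variation in the residual error and makes the interval for the treatment difference slightly wider than necessary. The titration weeks fill more of a 6-month window than of a 12-month one, so any effect should be larger at 6 months. Only precision is at stake: randomisation protects the estimate from bias with or without the extra covariate.

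**Working it through.** **Inputs from Sample size and power calculations.** The difference is 10 points, with 90% power and 5% significance ("we assume a 10% difference in 12-month TTR with 90% power and 5% significance level for our sample size calculation"). The test is two-sided, and the SD is 26 ("using an SD of ‘26’ as observed in a previous Thai study"). The result is "sample size for randomisation in a 1:1 ratio would be 288 or 144 per arm".

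**The plan's own figure.** By the normal approximation, n per arm = 2 × (1.960 + 1.282)² × 26² / 10² = 142.1, so 143. With the noncentral t distribution, power is 89.99% at 143 per arm and 90.19% at 144, so 144 per arm (288) reproduces. Allowing for 10% attrition, 288 / 0.9 = 320, also as stated. The SD carries no reduction for covariates, so the 90% does not depend on any adjustment.

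**Effect of a further covariate.** Let R² be the share of TTR variance it explains beyond centre, sex and score. The article gives no value, so R² is an assumption. The residual SD is 26 × √(1 − R²), the standard error of the difference is that SD × √(2/144), and the 95% half-width is 1.96 times the standard error.

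- R² = 0: 26 × √(2/144) = 3.064; half-width 6.01.
- R² = 5%: 26 × √0.95 = 25.34; 25.34 × √(2/144) = 2.987; half-width 5.85.

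**Cost of the added terms.** In a randomised comparison of N = 288, k added terms raise the expected variance of the treatment difference by about k/(N − k − 3), because of chance imbalance in those terms. That is 1/284 = 0.35% for one term and 3/282 = 1.06% for three. Residual degrees of freedom become 286 − k. The existing covariates are left out of both sides of the comparison for simplicity.

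| Assumed R² at 12 months | Half-width before cost (TTR points) | Power before cost | Power, one term | Power, three terms |
|---|---|---|---|---|
| 0 | 6.01 | 90.2% | 90.1% | 89.9% |
| 1% | 5.98 | 90.5% | 90.4% | 90.2% |
| 2% | 5.95 | 90.8% | 90.7% | 90.5% |
| 5% | 5.85 | 91.6% | 91.5% | 91.3% |

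Three terms cost about 0.3 power points and one term about 0.1. At R² = 1%, three terms bring power back to the 90.2% of the plan.

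**How plausible the range is.** Simulated INR paths can only illustrate this, because the ramp, noise and dose-error settings are invented.

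- With early dose error titrated away and mean TTR about 46–61%, baseline INR plus days on warfarin explained about 1–4.5% at 12 months and 2–10% at 6 months.
- Days on warfarin alone explained 0–0.4% at 12 months.
- Other settings, with mean TTR near 50% and the INR taken on warfarin at randomisation, gave about 4–7% at 12 months and 8–12% at 6 months. This fell to about 1–4% if every patient started warfarin at randomisation, and to near zero if the INR predated warfarin.

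The first set did not simulate centre, sex and score, so the share beyond those terms could be smaller.

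**The case against.** The strongest reply is that nothing here is wrong. Adjusting for the stratification factors is correct and agrees with the randomisation scheme, the sample size reproduces without further covariates, and an analysis plan that is not shown may name more. All of this stands, and it is why the point is an optional improvement.

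The reply also says that any gain is assumed. That stands too. The article reports no association between baseline INR and TTR, and it does not say whether the baseline INR is taken before warfarin or at randomisation. In the first case it would vary little and explain almost nothing. The start of the TTR window is not stated either. This does not make adjustment invalid, since a value from before randomisation cannot be affected by allocation.

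Two stronger readings are tempting. A reader might infer that the 28-day amendment itself costs precision; but days on warfarin explain almost nothing in the simulations, and any useful information lies in the INR. A reader might also assume an R² of 10% or more for the primary outcome. The documents do not support that. Simulated 12-month values that high came only from runs with mean TTR of 32–46%, below the 50–55% the protocol cites, and the other values of about 10% concern TTR at 6 months.

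It is also fair to say that a chance imbalance in early INR is no defect, because the planned interval already allows for it. Nor is the change wholly free: it adds terms to the primary model of an open-label trial with annual interim analyses, so its timing has to be documented.

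**Conclusion.** A small, optional efficiency point. The covariate set is valid, gives no bias and leaves the planned power intact. If the INR at randomisation explains 1–5% of 12-month TTR variance beyond centre, sex and score, power at 144 per arm moves from 90.2% to about 90.5–91.6% before the cost of the terms. The half-width narrows from 6.01 to between 5.98 and 5.85 points, against a 10-point target. With three terms there is no net gain at 1%; with one term a small gain remains. The benefit may be larger for TTR at 6 months and almost nil if the baseline INR was taken before warfarin.

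These figures rest on an assumed R², SD 26 and 144 evaluable patients per arm. They apply only to the linear model, because the Mann-Whitney fallback uses no covariates. The documents do not show that precision is lost, only that some may be left unused.

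**What to change.** Before anyone involved in the analysis sees outcome data by arm, prespecify the most recent INR at or before randomisation as a covariate in the linear models for TTR at 12 and 6 months, alongside centre, sex and score. One suitable form is the absolute distance from 2.5, the middle of the target range. State when this INR is taken and when the TTR window starts. Replace missing baseline values with the overall mean, calculated without regard to arm, so that no patient is dropped. Keep the model with stratification factors only as a sensitivity analysis. Days on warfarin is optional and adds little.

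The cost is one or two degrees of freedom, about 0.1 power points per term if the term turns out to be uninformative, and a dated, documented change to the analysis plan. It needs no new visits or patients and uses an INR that Table 2 already schedules.

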#### Subgroup analysis

Subgroup analyses will be conducted for the stratification variable sex only. All other stratification variables will be used only to ensure that the two groups are balanced in terms of these important variables. Subgroup analyses will be limited to the primary outcome only. Tests for statistical heterogeneity (eg, by including the treatment group by subgroup interaction parameter in the regression model) will be performed prior to any examination of effect estimates within subgroups. The results of subgroup analyses will be treated with caution and will be used for the purposes of hypothesis generation only.

#### Missing data and sensitivity analyses

Missing and ambiguous data will be queried using a data clarification system, and will focus on data required for trial outcome analysis and safety reporting. Every attempt will be made to collect full follow-up data on all study participants. A sensitivity analysis will be performed on the primary outcome measure only to examine the possible impact of any missing data for the primary outcome. This will include the use of multiple imputation using chained equations. Further sensitivity analysis will also be done if a substantial number of participants do not comply with randomised allocated group and so a per-protocol analysis may also be conducted. Any sensitivity analyses will not, irrespective of their differences, supplant the planned primary analyses.

#### Interim analysis

Interim analyses of safety and efficacy for presentation to the independent DMC will take place during the study. The committee will meet prior to study commencement to agree the manner and timing of such analyses. The analysis of the primary and major secondary outcomes and full assessment of safety (adverse events and serious adverse events) will be performed at annual intervals. Criteria for stopping or modifying the study based on this information will be ratified by the DMC.

#### Planned final analyses

The final analysis for the study will occur once the last randomised participant has completed the 12-month follow-up and any corresponding outcome data have been entered onto the study database and validated as being ready for analysis.

#### Withdrawal

Patients may withdraw consent from the study at any time. Patients may also withdraw from trial treatment but continue with study follow-up and data collection as per the protocol. If the withdrawal is initiated by a healthcare professional, full details for the reason for withdrawal will be recorded on the case report forms. In all other cases, a simple statement reflecting the patient’s preference will be noted. The patients who are switched to NOACs will be followed for clinical events. The INR data will be collected to the end of warfarin treatment for the TTR calculation and analysis as ITT analysis.

#### Analysis of outcome measures

##### Primary outcome

The primary outcome is the TTR at 12 months and differences in TTR between the intervention and usual care groups will be examined using a linear regression model. Results will be presented as mean difference and 95% CI. A key assumption for this analysis is that the data will be normally distributed; this assumption will be examined visually based on the residuals from the fitted model. If data are deemed not to be normally distributed, then the Mann-Whitney U test will be used for analysis.

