##### Secondary outcomes

The secondary endpoints for the trial includes continuous, categorical and time-to-event data items. Any secondary endpoints that are continuous in nature will be analysed in the same way as described for the primary outcome. For dichotomous secondary endpoints, the proportion of participants and percentages will be compared between arms using a log-binomial model. Relative risks and 95% CIs will be calculated. For any time-to-event outcomes these will be compared between treatment arms by using survival analysis methods. Cox proportional hazards model will be used and treatment effects will be expressed as HRs with 95% CIs. Kaplan-Meier survival curves will be constructed for visual presentation of time-to-event comparisons.

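### If residuals look non-normal, the primary TTR analysis becomes an unadjusted Mann-Whitney test that does not address the mean difference the trial is sized on

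*Protocol article*

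**What the plan says.** Under Primary outcome, the article specifies a linear regression for TTR at 12 months and states: "Results will be presented as mean difference and 95% CI". Normality is to be judged by eye from the residuals of the fitted model. The section then says: "If data are deemed not to be normally distributed, then the Mann-Whitney U test will be used for analysis".

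Under Statistical analysis: "All outcomes will be adjusted for the stratification variables", namely centre, sex and baseline score, with a closing qualifier that limits this to where it can be done. The same section undertakes to give between-group differences, with mean differences as an example, with CIs and p values for all major outcomes.

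Under Secondary outcomes: "Any secondary endpoints that are continuous in nature will be analysed in the same way as described for the primary outcome".

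The sample size is set "to detect a 10% mean difference in TTR at 12 months", so the quantity powered is a difference in means.

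**The concern.** The plan names two primary analyses that are not equivalent, and a judgement made after the outcome model is fitted decides between them. The treatment estimate already exists by then.

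The fallback answers a different question. Mann-Whitney asks whether a patient drawn from one arm tends to have a higher TTR than one drawn from the other. That matches a comparison of means only if the arms differ by a pure shift. A pure shift is doubtful on a 0–100 scale. It is more doubtful here because about 15–20% of patients are expected in Group 2a, where the intervention arm receives usual care only.

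The plain test also cannot use the stratification factors and produces no mean difference. Any mean difference reported beside it would carry an interval that does not correspond to the primary p value. The planned sex-by-treatment interaction, described with a regression model as the example, would then sit beside a primary result from another framework.

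**Working it through.** **1. The protocol's own sample size.** Inputs from Sample size and power calculations: "we assume a 10% difference in 12-month TTR with 90% power and 5% significance level"; "using an SD of ‘26’ as observed in a previous Thai study"; "using two-sided test, sample size for randomisation in a 1:1 ratio would be 288 or 144 per arm".

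n per arm = 2(1.960 + 1.282)² × 26² / 10² = 2 × 10.51 × 6.76 = 142.1, so 143. The t-based solution is 143.03, which rounds up to the stated 144. Then 288 / (1 − 0.10) = 320. Both figures reproduce. Power at 144 per arm is 90.4%.

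**2. Is the trigger plausible?** A normal curve with SD 26 does not fit inside 0–100.
- Centred at 52.5: (0 − 52.5)/26 = −2.02 (2.2% below 0) and (100 − 52.5)/26 = 1.83 (3.4% above 100), in total about 6%.
- Centred at 62.5: −2.40 (0.8%) and 1.44 (7.5%), in total about 8%.

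Visible departure from normality is therefore plausible. The document gives no TTR distribution, so it is not certain.

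**3. Is the switch needed, and what does it change?** Simulation with 5,000 trials per scenario, 144 per arm, SD 26 in both arms and a 10-point effect for power and coverage. TTR is drawn from a beta distribution scaled to 0–100; that shape is an assumption. Monte Carlo error is about 0.3 points at 5% and 0.4 points at 90%. M-W is Mann-Whitney.

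| Control mean | Type I: means | Type I: M-W | Type I: smaller p | CI coverage: means | Power: means | Power: M-W |
|---|---|---|---|---|---|---|
| 50 | 5.1% | 4.9% | 5.3% | 94.8% | 89.5% | 89.4% |
| 52.5 | 4.7% | 4.8% | 5.0% | 95.4% | 90.4% | 91.0% |
| 55 | 4.5% | 4.5% | 4.9% | 95.1% | 90.4% | 92.0% |

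A Shapiro test rejected normality in all 500 samples checked per scenario, yet the means comparison kept its error rate and coverage. (A Shapiro test is not the visual check that the protocol specifies.) A separate run of 6,000 trials at 52.5 versus 62.5 found the two tests agreeing on significance in 98.6% of trials.

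**4. What the lost adjustment costs.** Let R² be the share of variance explained by the stratification factors. The protocol gives no value, so 0–20% is an assumed range. For the adjusted model, power ≈ Φ(10 / [26√(1 − R²) × √(2/144)] − 1.96).
- R² = 0: SE = 3.064; 3.26 − 1.96 = 1.30; 90.4%.
- R² = 0.10: SE = 2.907; 3.44 − 1.96 = 1.48; 93.1%.
- R² = 0.20: SE = 2.741; 3.65 − 1.96 = 1.69; 95.4%.

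Simulation with normal data and 24 equal strata (assumed) gives 90.3%, 92.7% and 95.1% for the adjusted model, against 88.9%, 89.4% and 91.1% for Mann-Whitney. The gap is 3.3 points at R² = 0.10 and 4.0 points at R² = 0.20. Because the test ignores the strata, its type I error falls to 3.6% at R² = 0.20.

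**The case against.** The strongest defence is that model, check and fallback are all named in advance, and that on the protocol's own figures the choice hardly matters to error rates or power. That stands. The finer criterion for the visual check could sit in an analysis plan that is not shown, so its absence from the article is not part of this point.

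Three stronger readings are tempting, and the document does not support them.
- **That the fallback breaks a firm requirement to adjust.** The adjustment sentence is qualified, so losing the adjustment is tolerated. It is a loss of precision, not a contradiction. The lost power is also a gain the plan never counted on: without adjustment, power returns to about the planned 90%.
- **That no mean difference would be reported.** The general commitment under Statistical analysis could still produce one. The defect is narrower: the estimate and its interval would not match the rank-test p value.
- **That the switch seriously inflates false positives.** With equal means of 65 and SDs of 30 and 18, Mann-Whitney rejects in 29% of simulated trials, against about 4% for the means test. This shows that the hypotheses differ, but the protocol gives neither that mean nor those SDs. With the same SDs at a mean of 52.5 the rate is about 6%. It is an illustration, not a forecast.

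The reach also has a limit. QALYs are covered by a separate bootstrap rule, so the secondary outcomes affected are those such as 6-month TTR, knowledge change and EQ-5D-5L scores.

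**Conclusion.** The point holds and should be fixed, but it does not threaten the trial's validity. If the fallback is triggered, the primary test stops addressing the powered mean difference, has no matching estimate or CI, and drops the stratification factors. Nothing else in the article repairs this.

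Under the protocol's central figures the effect on type I error and on the significance decision is negligible. The precision loss is about 3–4 points of power if the strata explain 10–20% of the variance, and about 1 point if they explain none. These sizes rest on assumed beta or normal shapes, equal SDs, the assumed strata and the assumed R². The objection to the estimand rests on none of them. The switch also buys nothing, since the comparison of means behaves properly at 144 per arm with a bounded outcome.

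**What to change.** Replace the conditional sentence with a fixed rule. The primary analysis is the linear regression adjusted for centre, sex and SAMe-TT2R2 score, whatever the residuals look like, with HC3 robust standard errors or a bootstrap CI for the mean difference. Report a rank test stratified by the randomisation factors (van Elteren) as a sensitivity analysis only. Apply the same rule to the continuous secondary outcomes.

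This fits the protocol's own approach under Health economics analysis, where skewed costs and QALYs are compared by bootstrapped means. The cost is a sentence or two in the protocol or analysis plan, settled before outcome data by arm are examined. The sample size stays at 288 evaluable and 320 randomised, and no extra data or patient burden is involved.
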